### Data collection storage and monitoring

Data will be collected by the research team members, and only individuals authorised by the chief investigator will have access to the data. All data will be processed in accordance with the General Data Protection Regulation 2016 and the Data Protection Act 2018. Data will be given a unique participant identification number. Data will be documented in paper-based case report form (CRF), all data will be uploaded to an access-controlled OneDrive folder from a password-protected computer and all paper documents will be stored in a locked cabinet. Data entry will be checked by two of the research team members to minimise errors. Data will be archived in accordance with institutional guidelines after study closure and will be stored up to 5 years. No formal data monitoring committees have been organised for this study. Research team members, led by the chief investigator, will monitor the study throughout the period of the research study.

### Data analysis methods

Initially, intention-to-treat analysis will be used, and all data will be used from all participants according to the groups to which they have been assigned to. Secondary analysis will involve per-protocol analysis, which will analyse the adherence to the intervention. All obtained data will be used for the analysis. To minimise missing data, participants will be contacted weekly by the research team if in the intervention group and call to all control participants for their follow-up visit as a reminder. As the study requires a single follow-up visit, only complete cases will be analysed, and no data imputation will be used. All statistical analyses will be carried out using the IBM SPSS software, version 28. Descriptive statistics will be presented as means and standard deviations (SD). All data will be assessed for normality using the Kolmogorov–Smirnov test. Independent samples *T*-test or Mann–Whitney *U*-test, as appropriate, will be used to assess the differences in variables between COVID and non-COVID groups. Paired-samples *T*-test or Wilcoxon signed-rank test, as appropriate, will be used to evaluate the differences in variables pre- and post-intervention. Pearson’s or Spearman’s tests (as appropriate) will be used to determine correlation coefficient (*r*). A *p*-value of < 0.05 will be considered statistically significant.

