### Sample size

One hundred twenty participants aged between 50 and 85 years will be recruited for the study. This will include 80 participants with a history of COVID-19 and 40 healthy individuals without a history of COVID-19 to complete baseline assessments. Additionally, participants with a history of COVID-19 will be randomly assigned (1:1) to either a 12-week home-based physical activity intervention or usual care control group. The study design is outlined in Fig. 2. The primary outcome measure is LV GLS, as a measure of cardiac systolic function. With a type I error of 0.05 and an intended high power of > 90%, 40 participants per group are required to detect a 3% difference in LV GLS between the COVID-19 and non-COVID groups. In response to the physical activity intervention within the COVID-19 group, assuming a standard deviation of 2.5% and an estimated attrition rate of ~ 20% in the intervention period of the study, 40 participants per group will be required, providing the overall recruitment target of 80 participants with a history of COVID-19.

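### The lead analysis is called intention-to-treat on all participants, but the same paragraph limits it to complete cases, so about 16 of 80 randomised participants would be left out

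*Protocol article*

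**What the plan says.** Three statements in the Data analysis methods section of the protocol article bear on who is analysed.

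- The lead analysis: "Initially, intention-to-treat analysis will be used, and all data will be used from all participants according to the groups to which they have been assigned".
- After a sentence on the secondary per-protocol analysis: "All obtained data will be used for the analysis".
- The missing-data rule, for which the single follow-up visit is given as the reason: "only complete cases will be analysed, and no data imputation will be used".

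The same section describes how missing data are to be kept down: "participants will be contacted weekly by the research team if in the intervention group", while control participants get a call to remind them of the follow-up visit.

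Three other sections matter. Outcome measures defines the primary outcome as the mean change in LV GLS after 12 weeks. Sample size plans the randomised comparison "assuming a standard deviation of 2.5% and an estimated attrition rate of ~ 20% in the intervention period of the study", with 40 per arm and 80 in total. Study assessments adds that anyone who becomes ineligible during the study is withdrawn.

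**The concern.** The article promises an analysis of every randomised participant and then sets a rule that removes everyone without a 12-week measurement. With one post-baseline visit, a missed visit means no primary outcome at all, so the two statements part company as soon as one person is lost. The plan expects a fair number to be lost.

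The label matters because readers take intention-to-treat on all participants to mean that the balance created by randomisation has been kept. A completers' analysis keeps that balance only under an assumption about why people are missing, and the article states none. The reason it gives, the single follow-up visit, describes the design. It does not say why those who miss the visit can be ignored.

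The arms are also contacted differently during follow-up, weekly against a reminder call, so unequal loss is plausible.

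**Working it through.** **Inputs**

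- Randomised: 80, allocated 1:1, so 40 per arm (Sample size).
- Expected attrition in the intervention period: about 20% (Sample size).
- SD: 2.5 percentage points of strain (Sample size).
- Primary outcome: 12-week change in LV GLS (Outcome measures).
- Missing-data rule: complete cases, no imputation (Data analysis methods).

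**The plan's own figure**

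The stated 40 per arm fits 32 completers inflated for 20% loss: 32 / (1 − 0.20) = 40. How 32 would have been reached cannot be checked, because the article gives no target difference for the randomised comparison. That is a separate matter. What counts here is that the stated size is consistent with a plan built around 32 completers per arm.

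**Who is left out**

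- Expected loss: 80 × 0.20 = 16.
- Analysed: 80 − 16 = 64, or 40 × 0.80 = 32 per arm if loss is equal.

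**Do the two rules agree?**

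| Rule | Set it implies for the primary outcome |
|---|---|
| Intention-to-treat, all participants as assigned | 80 |
| Complete cases, no imputation | about 64 |

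They coincide only with no loss at all.

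**Power**

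With SD 2.5, two-sided α = 0.05 (the article does not state sidedness) and 90% power, the normal approximation for the detectable difference is 2.5 × (1.960 + 1.282) × √(2/n):

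- n = 32: 2.03 points.
- n = 40: 1.81 points.

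The second value is a bound that no missing-data method would reach, since none recovers unobserved follow-up values. An allowance for attrition protects power. It does nothing about bias.

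**Possible bias (illustration only)**

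Let p be the share lost in an arm, C the completers' mean change, and g the gap between completers and dropouts. The full-arm mean is (1 − p) × C + p × (C − g) = C − p × g, so the completers' mean is off by p × g. Assume p = 0.20 and a gap of 0.5 to 1 SD (1.25 to 2.5 points) in one arm only:

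- 0.20 × 1.25 = 0.25 points.
- 0.20 × 2.5 = 0.50 points.

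The bias in the between-arm difference is p₁g₁ − p₀g₀. If loss and gap are the same in both arms it is zero. The gap is assumed; the article has no data on it.

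**The case against.** A fair defence reads the intention-to-treat sentence as being about assignment: analyse people in their allocated arm whatever their adherence, in contrast to the per-protocol analysis that follows, and use whatever data were obtained. The complete-case rule is stated openly in the same paragraph, so nothing is hidden. This shows that the fault is largely one of labelling. It does not remove the fault, because the sentence promises data from all participants and the later rule takes some of them out.

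A second defence is statistical. With one follow-up there are no intermediate LV GLS values to impute from. If missingness depends only on arm and measured baseline variables, a complete-case model adjusted for those variables is valid, and imputing from the same variables adds little. This stands. A reader might infer that multiple imputation must be the primary analysis, but the documents do not force that. Imputation under missing-at-random would also not remove the bias illustrated above if baseline variables do not explain the gap. A delta-adjusted analysis is what examines it. The tests listed in the article are, however, unadjusted, so the condition that would make complete cases valid is not built in.

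A third defence is that missing-data sensitivity analyses belong in a statistical analysis plan that is not shown. Their absence from an article is indeed no fault in itself. But the article goes further and rules imputation out, so a later plan that allowed it would contradict the article.

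A reader might also infer that people who fail the walking programme will be the ones who miss follow-up, or that the contact schedule will cause unequal loss. The documents show neither. The weekly calls are part of the intervention as well as a retention measure, controls do get a reminder, and both arms are invited back. Finally, step logs might look like useful imputation variables, but nothing says they will be recovered from people who do not return.

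**Conclusion.** The contradiction is real and lies in stated rules, not in missing detail. Followed as written, the complete-case rule gives a completers' analysis of about 64 of 80 randomised participants, and it should not be presented as intention-to-treat on all participants. The 16 is a planning estimate, and it concerns only the randomised part of the study, not the baseline comparison of people with and without a history of COVID-19.

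The main cost is possible bias, not lost power. Its size is unknown. The 0.25 to 0.50 points rests on 20% loss, a gap of 1.25 to 2.5 points in one arm, and no such gap in the other. It is tempting to express this as a percentage of the effect the trial seeks, but the article states no target difference for the randomised comparison, so any such percentage would rest on a benchmark chosen by the reader. Unequal loss between arms is plausible, not shown. The change should be made because it corrects a misleading label at little cost.

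**What to change.** In the Data analysis methods section:

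1. Name the primary set as randomised participants with an observed 12-week LV GLS, analysed in the arm to which they were assigned, and drop the claim that it contains all participants.
2. State the primary test as a between-arm comparison of 12-week LV GLS adjusted for baseline LV GLS.
3. Replace the bar on imputation with a sensitivity analysis on all 80 randomised participants: multiple imputation by arm from baseline variables, then delta-adjusted (tipping-point) departures that show how different the dropouts would have to be to change the conclusion.
4. Give both arms the same follow-up appointment reminder, apart from the weekly intervention calls.

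Making multiple imputation on all 80 the primary analysis, with complete cases as the sensitivity analysis, would also resolve the contradiction. It is an option, not a requirement.

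The cost is some extra analysis work and a possibly wider interval in the sensitivity analysis. The recruitment target need not change.

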### Outcome measures

The primary outcome measure is mean change in left ventricular global longitudinal strain after 12 weeks of the study intervention. Secondary outcomes are mean changes from baseline to the end of the intervention period in arterial stiffness (pulse wave velocity and augmentation index), measures of systolic and diastolic function of the heart (i.e. left ventricular ejection fraction, cardiac output, stroke volume, cardiac power, early-to-late filing ratio, right ventricular global longitudinal strain, left atrial strain, ventricular-arterial coupling, right ventricular diastolic function), heart rate variability, functional capacity, lung function, inflammatory and cardiac biomarkers, quality of life and well-being (depression, anxiety, stress, fatigue and sleep measures). Sleep measures include bedtime (h:min), wake-up time (h:min), time-in-bed (h), total sleep time (h), sleep onset latency (min), sleep efficiency (%), number of awakenings and wake after sleep onset (WASO, min), number and timing of naps, inter-daily variability and stability (as markers of circadian rhythmicity), and timing and nature of light exposure during a 24-h period. Additionally, we will assess the differences in the COVID-19 group vs. the non-COVID-19 group.

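### A Kolmogorov-Smirnov pre-test lets the data decide whether the mean change in LV GLS is tested as a mean; separately, the 80 versus 40 comparison needs a test that allows unequal variances

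*Protocol article*

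**What the plan says.** Outcome measures: "The primary outcome measure is mean change in left ventricular global longitudinal strain" after 12 weeks of the intervention. This outcome belongs to the participants with a history of COVID-19, randomised 1:1. The same section then adds, as a further comparison, COVID-19 versus non-COVID-19.

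Sample size: the study enrols "80 participants with a history of COVID-19 and 40 healthy individuals without a history of COVID-19". The calculation is framed as a difference in LV GLS: "40 participants per group are required to detect a 3% difference in LV GLS between the COVID-19 and non-COVID groups". For the intervention part it assumes an SD of 2.5% and attrition of about 20%. No SD is given by group.

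Data analysis methods: "All data will be assessed for normality using the" Kolmogorov-Smirnov test. An independent-samples t-test or a Mann-Whitney test, as appropriate, "will be used to assess the differences in variables between COVID and non-COVID groups". A paired t-test or a Wilcoxon signed-rank test, again as appropriate, is listed for values before and after the intervention. A p-"value of < 0.05 will be considered statistically significant". The section gives no criterion for appropriateness other than the normality check, and does not say whether the t-test pools the variances.

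**The concern.** The outcome is defined as a mean and the sample size rests on a difference with an SD, but the test is chosen after the data have been seen. The Wilcoxon signed-rank test asks whether changes are distributed symmetrically about zero. For skewed changes that is a different question from whether the mean change is zero. The quantity behind the primary result would therefore depend on a preliminary test with its own error rate, and the switch is most likely under skewness, where the two questions differ.

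A second, separate matter concerns the baseline comparison. The groups are planned at 80 and 40. With unequal group sizes, a pooled-variance t-test has the wrong standard error whenever the two SDs differ. Nothing in the protocol gives a reason to expect equal spread in people with and without a history of COVID-19.

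**Working it through.** **Inputs from the protocol.** Significance level 0.05 (taken as two-sided). Group sizes 80 and 40 at baseline. Randomised arms of 40, or 40 × 0.8 = 32 after 20% attrition.

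**Assumed, because the protocol does not give them.** The pre-test is run at 5% with Lilliefors critical values (mean and SD estimated from the data). A failed check leads to the rank test. Distribution shapes and SD ratios are illustrative. Simulations used 20,000 runs per scenario, so the Monte Carlo standard error at 5% is √(0.05 × 0.95 / 20,000) ≈ 0.15 percentage points.

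**Step 1: is the plan's 5% reproduced when the groups have the same distribution?** Yes. At 80 versus 40 the two-stage rule gives 5.0% (normal), 4.9% (t with 3 df), 5.1% (gamma(4)), 4.8% (lognormal, σ 0.5), 5.1% (exponential) and 4.8% (lognormal, σ 1).

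**Step 2: how often does the rule switch when the data are truly normal?** One sample is checked at 5%, so about 5% of the time (4.8% simulated at n = 32 and 40). If each of two groups is checked: 1 − 0.95² = 9.75%, or about 10% (9.9% simulated at 80/40).

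**Step 3: pre/post test when the true mean change is zero.** Percentage of trials with p < 0.05:

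| Shape of the changes | n | Pre-test fails | Paired t throughout | Wilcoxon throughout | Two-stage rule |
|---|---|---|---|---|---|
| Normal | 32 | 4.8 | 5.0 | 4.9 | 5.0 |
| Normal | 40 | 4.8 | 4.7 | 4.8 | 4.8 |
| Gamma(4) | 32 | 27.7 | 5.7 | 8.0 | 7.0 |
| Gamma(4) | 40 | 33.6 | 5.7 | 8.7 | 7.7 |
| Exponential | 32 | 81.8 | 7.1 | 17.0 | 16.4 |
| Exponential | 40 | 89.8 | 6.7 | 19.7 | 19.2 |

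Repeat runs put the paired t-test at 5.4-5.8% for gamma(4) and about 7% for the exponential. Under skewness the pre-test moves a test of the mean further from 5% than leaving the t-test alone. The excess grows with n, because the pre-test fails more often and Wilcoxon more readily detects that the median is not zero.

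**Step 4: COVID-19 versus non-COVID-19, 80 versus 40, normal data, equal means.** The true variance of the difference is s₁²/80 + s₂²/40. The pooled test uses [(79 s₁² + 39 s₂²)/118] × (1/80 + 1/40). The two-sided critical value on 118 df is 1.980.

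- SD 2 in the 80 and 3 in the 40. True: 4/80 + 9/40 = 0.275. Pooled: (316 + 351)/118 × 0.0375 = 0.212. Ratio of standard errors: √(0.212/0.275) = 0.878. Effective critical value: 1.980 × 0.878 = 1.739, a two-sided normal tail of about 8.2%.
- SD 3 in the 80 and 2 in the 40. True: 9/80 + 4/40 = 0.2125. Pooled: (711 + 156)/118 × 0.0375 = 0.2755. Ratio: 1.139. Effective critical value: 2.255, a tail of about 2.4%.

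Simulation with the same SD ratio of 1.5 (% of trials with p < 0.05):

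| Larger SD in | Pooled t | Two-stage rule | Welch |
|---|---|---|---|
| Group of 40 | 8.7 | 8.8 | 5.2 |
| Group of 80 | 2.7 | 2.9 | 5.1 |
| Neither | 4.9 | 5.0 | 5.0 |

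The pooled t and two-stage columns nearly coincide, so the pre-test plays almost no part here. At 40 versus 40 with the same SD ratio, the pooled t-test gives 5.1% and the two-stage rule 5.3%.

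**The case against.** The article never says outright that a failed check leads to ranks, at what level it is judged, or whether it is applied per group. Whether the t-test pools variances is detail that a full protocol or analysis plan may hold. SD ratios of 1.5 and exponential changes have no source in the protocol. With normal data of equal spread, the rank test addresses the same null at about 5%. Choosing Welch, robust errors or log transformation is partly a matter of preference.

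Much of this stands and limits the point. The error rates in steps 3 and 4 are conditional illustrations. What remains is that a normality check on all data, followed by paired alternatives with no other criterion, reads as a switching rule, and that rule conflicts with an outcome defined as a mean.

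A reader might infer three stronger things that the documents do not support:

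- **That the pre-test makes the 80 versus 40 test miss 5%.** With equal distributions the rule holds at 4.8-5.1%. Under unequal SDs with normal data, the distortion comes from pooling variances across unequal groups.
- **That the 80:40 imbalance affects the primary outcome.** The mean change after 12 weeks concerns the 1:1 randomised arms. The 80 versus 40 contrast is a separate baseline comparison.
- **That about 10% of randomised between-arm comparisons would switch.** The article lists no two-sample test between the arms. The two-group figure applies to COVID-19 versus non-COVID-19, and the pre/post test has the single-sample rate of about 5%.

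**Conclusion.** The point holds in two separate parts.

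First, the data decide whether the primary outcome is analysed as the mean it is defined to be. This follows from the article's own text and needs no distributional assumption. Its effect on error is nil for normal changes. For skewed changes the rule rejects a true zero mean change in about 7% of trials under moderate skewness (gamma(4)) and 16-19% under the exponential, which is an extreme case and not a forecast for LV GLS.

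Second, if the baseline contrast uses a pooled-variance t-test, its error is about 8% or about 2.6% when one group's SD is 1.5 times the other's, depending on whether the smaller or the larger group is more variable. It is about 5% when the SDs are equal. The documents neither state nor exclude unequal SDs.

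The analysis should be changed. Neither part shows that the planned study is invalid.

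**What to change.** Delete the normality pre-test as a rule for choosing tests. Prespecify one mean-based analysis for LV GLS and the other continuous outcomes:

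- **Randomised arms:** a baseline-adjusted linear model for the 12-week change, reporting the difference in mean change with its confidence interval.
- **COVID-19 versus non-COVID-19:** a Welch t-test, or a linear model with robust standard errors.
- **Right-skewed biomarkers:** name in advance those to be log-transformed.
- **Rank tests:** keep them as labelled sensitivity analyses.

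The cost is wording only, since the planned software already provides Welch tests and linear models. When the SDs are equal, Welch's interval is negligibly wider.

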Cardiovascular involvement in healthy individuals with a history of COVID-19 infection is still uncharacterised. It is important to investigate the initial signs of changes in cardiovascular structure and function to improve understanding of the effects of this novel disease. This can inform health care services by providing evidence for the need for comprehensive cardiovascular screening and early interventions to prevent deterioration if cardiovascular function in people with a history of COVID-19.

The present study is designed to evaluate the effects of COVID-19 on cardiovascular structure and function and to determine their amelioration with physical activity. The aim of the present study is twofold: (i) to define the effect of COVID-19 on cardiovascular function (i.e. arterial stiffness, cardiac systolic and diastolic function) in otherwise healthy individuals and (ii) to evaluate the effect of a home-based physical activity intervention on cardiovascular function in people with a history of COVID-19. We will test the following two hypotheses: (i) cardiovascular function will be significantly reduced in people with a history of COVID-19, and (ii) a home-based physical activity intervention will significantly improve cardiovascular function and quality of life in people with a history of COVID-19.

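### No stated test compares the two randomised arms; the intervention question is given only a pre/post test

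*Protocol article*

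**What the plan says.** The Sample size section states that "participants with a history of COVID-19 will be randomly assigned (1:1) to either a 12-week home-based physical activity intervention or usual care control group". The Introduction gives the matching hypothesis, that "a home-based physical activity intervention will significantly improve cardiovascular function and quality of life in people with a history of COVID-19". Under Outcome measures, "The primary outcome measure is mean change in left ventricular global longitudinal strain after 12 weeks of the study intervention"; no contrast between arms is attached to it. The only between-group comparison named there is the non-randomised one: "Additionally, we will assess the differences in the COVID-19 group vs. the non-COVID-19 group".

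The Data analysis methods section then gives tests to questions:

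- Independent-samples t-test or Mann–Whitney test: these "will be used to assess the differences in variables between COVID and non-COVID groups".
- Paired-samples t-test or signed-rank test: the "Wilcoxon signed-rank test, as appropriate, will be used to evaluate the differences in variables pre- and post-intervention".
- Pearson or Spearman coefficients: correlations.

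The same section opens with an intention-to-treat statement, under which "all data will be used from all participants according to the groups to which they have been assigned to". It also has all data checked for normality by the Kolmogorov–Smirnov test, with rank tests as the alternative.

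**The concern.** Randomisation supports a causal claim only through the contrast between the arms. A paired test asks a different question: whether strain moved from zero change over the roughly 13 weeks between visits. It answers yes for any cause of movement. Several causes that would act on both arms are plausible here. Table 1 admits participants from 28 days after infection, so natural recovery may still be under way. Regression to the mean and familiarity with repeat testing act on everyone. Control participants also wear a pedometer and log their steps, so their behaviour may change too. The control arm exists to subtract all of this, and the stated test does not use it for that purpose.

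The likely informal repair is to run the paired test in each arm and compare the p-values. That is not a test of the difference between arms, and under a common drift it can favour the intervention far more often than 2.5% of the time.

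A lesser point concerns the normality check. It lets the data switch the primary test to ranks although the primary outcome is defined as a mean change.

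**Working it through.** **1. Is there a between-arm test anywhere?** The two-sample tests are tied to COVID versus non-COVID. The paired tests are within-participant by construction. The correlations are not a comparison of arms. The intention-to-treat statement fixes who is counted in which arm but names no contrast, estimate or test. The text does not say whether the paired test is run in one arm, in each arm or pooled; none of the three compares intervention with control.

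**2. The plan's own sample size.** The article gives 40 per group, alpha 0.05, power above 90%, SD 2.5 and attrition of about 20%. It gives a 3-point difference for COVID versus non-COVID only, and no difference for intervention versus control. Combining the 3 points with the SD of 2.5 (two-sided):

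n = 2 × 2.5² × (1.960 + 1.282)² / 3² = 14.6, so 15 per group; 15 / 0.8 = 18.75, so 19.

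This does not reproduce 40. That is a separate matter, because the 3 points and the SD are stated for different comparisons. What matters here is that 40 × 0.8 = 32 completers per arm remain.

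**3. What the paired test does when the programme has no effect.** Assumptions not in the article: both arms drift by the same amount *d* in the direction of improvement, and the SD of change is 2.5 (the article does not say whether its SD is of a level or of a change). As a second case, take 2.5 as the SD of a level with an assumed pre/post correlation of 0.7, which gives an SD of change of 2.5 × √(2 × 0.3) = 1.94.

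The paired t statistic is noncentral t with 31 degrees of freedom and noncentrality *d*√32 / SD. For SD 2.5 and *d* = 0.5 this is 0.5 × 5.657 / 2.5 = 1.13; for *d* = 1.0 it is 2.26. With *p* the chance of significant improvement in one arm, the chance that the intervention arm is significant and the control arm is not is close to *p*(1 − *p*).

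| Common drift (points) | SD of change | Paired test significant, intervention arm | Significant in intervention, not in control |
|---|---|---|---|
| 0 | either | 2.5% | 2.4% |
| 0.5 | 2.5 | 19% | 16% |
| 1.0 | 2.5 | 59% | 24% |
| 1.5 | 2.5 | 91% | 8% |
| 0.5 | 1.94 | 29% | 21% |
| 1.0 | 1.94 | 81% | 16% |
| 1.5 | 1.94 | 99% | 1% |

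For a between-arm test the expected difference is *d* − *d* = 0 at every drift, so its rate in favour of the intervention stays at 2.5%.

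**4. Is the between-arm test affordable?** With 32 per arm and an SD of change of 2.5, the normal approximation gives a difference detectable at 90% power of 3.242 × 2.5 × √(2/32) = 2.03 points; the exact t calculation gives 2.06. Power is about 88% for 2 points and 99.7% for 3. If 2.5 is the SD of a level and the correlation is 0.5 (assumed), the SD of change is 2.5 × √(2 × 0.5) = 2.5 and the ANCOVA residual SD is 2.5 × √(1 − 0.25). The detectable difference then falls to 2.06 × √0.75 = 1.78 points.

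**The case against.** The strongest reply is that this is a condensed article. Randomisation to a usual-care arm, a sample size stated per group and analysis by assigned group all show that a between-arm comparison is intended, so the missing sentence may sit in a fuller document. The intention is credible. But the article is not silent on method: it names the test for the intervention and shows that a two-sample test was available, then gives that test to the other comparison. Someone following it would run the wrong analysis.

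Four narrower points stand:

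- The article never proposes comparing significance between arms; that is only a likely reading of two paired tests.
- The percentages depend on an assumed drift. With no drift neither reading is inflated, and the one-arm-only rate falls again at large drifts.
- Outcome assessors and analysts are unblinded. Bias from knowing the allocation can differ between arms, and a between-arm test would not remove it.
- ANCOVA is the more efficient choice rather than the only valid one. A two-sample test of change scores would also close the gap. A bootstrap interval and the removal of the normality check are improvements, not the core of the point.

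**Conclusion.** The concern holds and must be fixed. As written, no analysis tests the randomised comparison, and hypothesis (ii) would rest on a before/after change. This follows from the text alone and needs no numerical assumption. The size of the error does need assumptions. With 32 completers per arm, no true effect and a common improvement of 0.5 to 1.0 points, the false claim rate is 19% to 59% if the SD of change is 2.5, and 29% to 81% if it is 1.94, against 2.5% for a between-arm test. The planned sample is adequate for the correct test under the article's SD.

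**What to change.** In Data analysis methods, replace the paired-test sentence, so far as it concerns the intervention, with wording such as:

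> The primary analysis compares LV GLS at the follow-up visit between intervention and control by ANCOVA, adjusted for baseline LV GLS. The result is the adjusted between-arm mean difference with its 95% confidence interval and two-sided p-value. The method does not depend on a normality pre-test; a bootstrap confidence interval is a sensitivity analysis. Continuous secondary outcomes use the same model. Within-arm changes are descriptive only.

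In Outcome measures, state that the primary outcome is compared between intervention and control. In Sample size, state the between-arm difference that the 40 per arm is meant to detect.

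The cost is a few sentences. No further data or participants are needed, since both strain measurements are already planned in both arms, and the model runs in the planned SPSS software.
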